### Statistical analysis, power, and sample size

Sample size calculations were based on results from a local registry (SEPHIA) data analysis including 40 post-MI patients attending CR at one of the study centers (Skåne University Hospital in Malmö). Out of the 40 patients included in the analysis, 73% participated in a hospital-based exercise program, on average 7 times (range 2–12) during an 8-week exercise period. The difference (Δ) in cardiac exercise capacity (W), measured using a symptom-limited bicycle ergometer test at 2–4 weeks post-discharge and after completing a hospital-based exercise program (around 3–6 months post-discharge), was calculated. The average difference was + 14.6 (± 15.6) W. With a power of 90%, a two-sided significance level of 0.05, and a least mean difference at 10 W (standard deviation (SD) ± 20 W) between groups, the estimated sample size was 150 patients: 50 patients in the usual care arm and 100 patients in the intervention arm. This included an intention-to-treat dilution effect based on a 40% loss of adherence in the intervention arm, an estimation based on our own feasibility study as well as other studies reporting adherence to eHealth interventions in CR [11, 13–15, 17]. The study is not powered to detect effects on major adverse cardiac events. As such, these analyses will only be exploratory.

Differences in outcomes between the control arm and intervention arm will be performed using an independent samples *t* test (continuous variables) and a chi-square test (categorical variables). If differences in baseline characteristics, number of follow-up visits, or telephone contacts are observed, linear and logistic regression analysis will be applied, adjusting for the observed differences between the two study arms.

A full study protocol and a Standard Protocol Items: Recommendations for Interventional Trials (SPIRIT) checklist (recommended items to address in a clinical trial protocol and related documents) are provided as additional files (Additional files 1 and 2).

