### Randomization

Randomization will be done using sealed envelopes containing information as to which arm the patient is randomized. The envelopes will be prepared by a member of our research team and subsequently mixed by another member of the team. Based on power calculations, the estimated sample size is 50 patients in each arm (for details, see the section on Statistical analysis, power, and sample size). However, due to expected loss of adherence in the intervention arm, we decided to double the size of the intervention arm. As such, 50 patients will be randomized to the control arm and 100 patients to the intervention arm.

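### The stated inputs (10 W, SD 20 W, two-sided 0.05, 100 vs 50 patients) give about 82% power, not 90%, and less if the 10 W has still to be diluted for non-adherence

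*Protocol article*

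**What the plan says.** The protocol article's section on statistical analysis, power, and sample size gives every input. The error rates are set as "With a power of 90%, a two-sided significance level of 0.05". The target and the result are given as "a least mean difference at 10 W (standard deviation (SD) ± 20 W) between groups, the estimated sample size was 150 patients", with 50 in usual care and 100 in the intervention arm. On adherence it adds: "This included an intention-to-treat dilution effect based on a 40% loss of adherence in the intervention arm". The comparison of continuous outcomes is an independent samples t test.

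The Randomization section describes how the number arose. First: "Based on power calculations, the estimated sample size is 50 patients in each arm". Then: "due to expected loss of adherence in the intervention arm, we decided to double the size of the intervention arm".

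The power section also reports registry data on 40 patients at one centre, with a mean gain of 14.6 W and an SD of 15.6 W. That SD is not the one stated for the calculation.

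**The concern.** The standardised difference is 10/20 = 0.5. A two-sided comparison at 90% power then needs roughly 85 patients per arm, so 50 per arm looked too small from the start, and doubling one arm looked unlikely to make up the gap as well as cover a 40% loss of adherence.

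The figure concerns the primary outcome. If the trial is reported as having 90% power when it has less, a non-significant result will be taken as stronger evidence against a 10 W benefit than the design can supply. Even on the kindest reading the type II error risk is about 18%, against the 10% implied.

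**Working it through.** **Inputs, all from the power section unless noted.** Difference 10 W; SD 20 W; two-sided alpha 0.05 (z = 1.960); power 90% (z = 1.282); 100 vs 50 patients; 40% loss of adherence. From the Randomization section: 50 per arm before doubling. Powers below use the noncentral t distribution; sample sizes use the normal approximation.

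**1. Attempt to reproduce the plan's figures.**
- 1:1 allocation: n per arm = 2 × ((1.960 + 1.282) × 20/10)² = 84.1, so about 85. The article has 50.
- 2:1 allocation: control n = 1.5 × ((1.960 + 1.282) × 20/10)² = 63.05, so 64 + 128 = 192. The article has 150, which is 42 fewer (22%).

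Neither 50 per arm nor 150 in total is reproduced, and no dilution has yet been applied.

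**2. Power at the planned size, 10 W as the ITT difference.**
- Standard error at 100/50: 20 × √(1/100 + 1/50) = 3.46 W. Ratio 10/3.46 = 2.89. Power 81.8% (normal approximation 82.3%).
- Standard error at 50/50: 20 × √(1/50 + 1/50) = 4.00 W. Ratio 2.50. Power 69.7%.
- Check of the 192: 128/64 gives 90.1%.
- Difference detectable with 90% power at 100/50: 11.3 W (11.2 W by the normal approximation).

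**3. Power if 10 W is the effect in adherent patients.** Let non-adherent patients gain a fraction f of the effect. The ITT difference is 10 × (0.6 + 0.4f). The article does not give f, so the values here are assumptions.

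| f | ITT difference | Power at 100/50, SD 20 W |
|---|---|---|
| 0 | 6 W | 40.6% |
| 0.5 | 8 W | 63% |
| 1 (no dilution) | 10 W | 81.8% |

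With f = 0, reaching 90% at 2:1 would need 176 + 352 = 528 patients.

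**4. What doubling one arm buys.** Two arms of 100 and 50 carry the information of 2/(1/100 + 1/50) = 66.7 per arm, a gain of 66.7/50 = 1.33. Diluting 10 W to 6 W multiplies the required size by 1/0.6² = 2.8; diluting to 8 W multiplies it by 1/0.8² = 1.56. Both exceed 1.33.

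**5. Other routes to 90%.**
- Counting only 60 adherent patients against 50 controls, 10 W, SD 20 W: 73.5%.
- One-sided 0.05, 100/50, 10 W, SD 20 W, no dilution: 89.3% (normal approximation). The text says two-sided.
- Registry SD of 15.6 W, 50 per arm, 10 W, no dilution: 88.8%, and 90% needs 52 per arm. The text says SD 20 W.
- Registry SD of 15.6 W, 100/50: 95.7% for 10 W and 59.7% for 6 W.

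Only departures from the stated inputs come close to 90% or exceed it.

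**The case against.** The strongest defence is that 10 W is described as a difference between groups and the dilution is said to be included, so 10 W may already be the ITT difference. Multiplying it by 0.6 would then dilute twice. This stands: on that reading the 41% does not apply, and the shortfall is 8 points (82% against 90%).

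It also stands that zero benefit in non-adherent patients is an extreme case. The article measures adherence as logging data at least twice a week, and a patient below that level would still be sent text messages and reminders. Partial benefit is plausible, so the 41% needs its condition stated beside it.

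A reader might go further in four ways that the document does not support.
- That the trial is more likely than not to miss a 10 W effect in users. This needs 10 W before dilution, no benefit in non-adherent patients and SD 20 W all together. With 6 W and the registry SD, power is 59.7%.
- That the two sections contradict each other on what the power calculation produced. They can be read as successive steps: 50 per arm, then one arm doubled to reach 150. The fault is that neither step reproduces at SD 20 W.
- That loss to the second ergometer test was ignored. A journal article may leave this to the full protocol, which it names as an additional file.
- That 50 per arm was calculated with the registry SD. The near match (52) suggests it, but the article does not say so.

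None of this restores 90%: the stated inputs fall short even on the kindest reading.

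**Conclusion.** The power statement is wrong as written. With the stated alpha, difference, SD and arm sizes, power is about 82% if 10 W is the ITT difference. This rests on no assumption beyond the article's own inputs and its t test. The 50 per arm given as the starting point has about 70%.

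The size of any further loss is conditional. If 10 W is the effect in adherent patients, power is about 41% with no benefit in the other 40% and about 63% with half the benefit. In both cases doubling the intervention arm does not offset the dilution. The article fixes neither the meaning of the 10 W nor the benefit in non-adherent patients, so the 41% is not a figure for the trial as such.

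**What to change.** Keep the 150 patients and the 2:1 split; recruitment closed in April 2018. Change the wording as follows:

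- State that 100 vs 50 patients with SD 20 W give about 82% power at two-sided 0.05 for an ITT difference of 10 W, and that the difference detectable with 90% power is 11.3 W.
- Say whether 10 W is before or after dilution. If before, give the diluted power with its assumption, for example about 41% if non-adherent patients gain nothing.
- Drop the statement that the sample size delivers 90% power after allowing for 40% loss of adherence.
- Interpret the primary result by its 95% CI against 10 W, so that a non-significant result is not read as excluding that difference unless the interval does.

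The cost is wording only. No patients are added and no analysis changes; the stated power becomes less favourable.

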### Usual care

All patients, in both the control arm and the intervention arm, will be offered participation in CR programs according to the usual routine at each center. The CR programs at the three study centers have approximately the same follow-up protocol, as they all report to the SEPHIA registry, which requires data registration at fixed time points. Minimally, the CR program includes five out-patient visits at the CR center. The patient’s first contact is with a CR nurse within 2–4 weeks from discharge (*t*1), closely followed by a first physiotherapist visit (*t*2) at which a symptom-limited bicycle ergometer test is performed (Fig. 2). A second nurse or physician visit (*t*3) is offered at 6–10 weeks post-discharge. A follow-up visit with a physiotherapist (*t*4) is offered when the patient has completed his/her exercise program at the CR center, usually around 3–6 months post-discharge. A second ergometer test is performed at the *t*4 visit. At 6–8 months, laboratory measures of lipids and glucose/HbA1c are performed (*t*5), followed by a telephone call in case of abnormal results. A last visit to a nurse (*t*6) is offered at 12–14 months after the index event. Information on lifestyle (exercise, daily physical activity, diet, and smoking), risk factor levels (blood pressure, weight, waist circumference, fasting plasma glucose, Hb A1c, serum lipids), and self-rated health (measured with the EQ-5D quality of life (QoL) questionnaire and a general self-rated health visual analog scale 0–100) are controlled at the nurse and physiotherapist visits according to Fig. 2 [19].

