**Fig. 2 Fig2:**
[figure not shown]
Standard Protocol Items: Recommendations for Interventional Trials (SPIRIT) figure for the study. Lifestyle counseling and assessments are done for all patients, i.e., in both the control and the intervention arms. *CCU* coronary care unit, *t*1 first nurse visit (2–4 weeks after the index event), *t*2 first physiotherapist visit (2–4 weeks after the index event), *t*3 second nurse visit (6–10 weeks after the index event), *t*4 second physiotherapist visit (4–6 months after the index event), *t*5 measurement of serum lipids and glucose/HbA1c (6–8 months after the index event) followed by a telephone call in case of abnormal test results, *t*6 third nurse visit (conducted 12–14 months after the index event)

All patients will be offered participation in the traditional CR program at each study center irrespective of whether they drop out of the current study (both arms) or do not fully engage in the study intervention (intervention arm).

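### The stated 90% power includes no allowance, in either arm, for patients who lack one of the two ergometer tests

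*Protocol article*

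**What the plan says.** All places are in the protocol article.

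- **Statistical analysis, power, and sample size.** The inputs are "a two-sided significance level of 0.05", 90% power, "a least mean difference at 10 W" and an SD of 20 W. The result is 150 patients, 50 in usual care and 100 in the intervention arm. The only allowance described is "This included an intention-to-treat dilution effect based on a 40% loss of adherence in the intervention arm". Continuous outcomes are to be compared with an independent-samples t test.
- **Randomization.** The calculation gave 50 per arm. The intervention arm was then doubled because of expected loss of adherence, and the control arm stayed at 50.
- **Primary outcome.** The outcome is the change in submaximal exercise capacity between the first and second physiotherapist visits (t2 and t4), so it needs both tests.
- **Usual care.** The t4 visit "is offered when the patient has completed his/her exercise program at the CR center". The text after Fig. 2 promises all patients the traditional program "irrespective of whether they drop out of the current study (both arms"), and names incomplete engagement with the intervention as a separate case.
- **Sizing sample** (same section as the calculation). "Out of the 40 patients included in the analysis, 73% participated in a hospital-based exercise program".
- **Trial status.** All 150 patients had been included by April 2018. So 150 counts included patients, not patients with a measured outcome.

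**The concern.** Non-adherence and a missing outcome are different losses. A patient who stops using the app but attends both tests still contributes a change in watts; the average effect shrinks and the sample does not. A patient who misses a test contributes nothing to a t test on change, and the standard error grows. The printed calculation addresses the first loss, in one arm, and says nothing of the second.

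The article itself separates the two events when it distinguishes leaving the study from not fully engaging with the app. It also makes the second test follow an exercise program that not every patient joins. Having both tests in all 150 patients is therefore a favourable assumption.

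The control arm matters most. It holds 50 patients, the number the calculation returned, and it limits the precision of the comparison. If tests are missing, a null result could be read against a 90% power that the analysed sample did not have.

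**Working it through.** **Inputs.** Two-sided alpha 0.05, power 90%, difference 10 W, SD 20 W, allocation 100 to 50 (all from the sample size section). The proportion lacking a test is not given; 10% and 20%, equal in both arms, are assumed here.

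**Step 1: the plan's own figure.** For 1:2 allocation, the control n is (1 + 1/2) × (1.960 + 1.282)² × (20/10)² = 1.5 × 10.51 × 4 = 63.04, rounded up to 64. That gives 64 + 128 = 192. For 1:1 allocation, 2 × 10.51 × 4 = 84.06, rounded up to 85 per arm. The printed 150 (or 50 per arm before doubling) is not reproduced. For this point the consequence is that, on the printed inputs, 150 holds no hidden reserve that missing tests could draw on.

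**Step 2: power for the patients who have both tests.** The standard error is SE = 20 × √(1/n₁ + 1/n₀), the noncentrality is 10/SE, and power comes from the noncentral t distribution with n₁ + n₀ − 2 degrees of freedom.

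| Assumed missing | Intervention / control | SE (W) | 10/SE | Power | Loss against complete data |
|---|---|---|---|---|---|
| 0% | 100 / 50 | 3.464 | 2.887 | 81.8% | – |
| 10% | 90 / 45 | 3.651 | 2.739 | 77.6% | 4.2 points |
| 20% | 80 / 40 | 3.873 | 2.582 | 72.6% | 9.2 points |
| 27% (upper bound) | 73 / 36 | 4.073 | 2.455 | 68.2% | 13.6 points |

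The 27% row takes the 100% − 73% who did not join a hospital-based program and supposes that none of them has a second test. The article does not report this.

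**Step 3: splitting the gap to 90%.** With complete data, 90 − 81.8 = 8.2 points are already missing. That part comes from Step 1 and has nothing to do with missing tests. Missing tests add 81.8 − 77.6 = 4.2 points at 10% and 81.8 − 72.6 = 9.2 points at 20%.

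**Step 4: does the dilution question change this?** The article does not make clear whether 10 W is the difference before or after dilution. If it applies to adherers and the 40% who stop gain nothing, the difference tested is 10 × 0.6 = 6 W. The same formula then gives 40.6% with complete data, 37.1% at 10% missing and 33.6% at 20%. The level is far lower, but missing tests still cost a similar 3.5 to 7.0 points.

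**The case against.** The case on the other side has five parts.

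1. **The article condenses a full protocol, supplied as an additional file that is not shown.** Attrition and missing-data rules often sit there or in an analysis plan, so their absence here is no error. That stands, and no such absence is charged. What remains is the printed claim: the article gives a power, says what the figure included, and attaches it to the number randomised.

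2. **The 73% is not a test-attendance figure.** A reader might infer that the plan's own data show 27% of patients without a second test. They do not. The 27% is non-participation in a hospital-based program among 40 registry patients. If all 40 contributed to the reported mean change of 14.6 W, the non-participants were tested twice, which points the other way. The text does not settle this, so 27% can serve only as an assumed upper bound.

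3. **The sentence on dropout is a promise of care, not a forecast.** A reader might infer that the plan expects a given level of dropout. It foresees the event in both arms and gives no rate.

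4. **t4 belongs to usual care.** It is among the visits offered to everyone, the Fig. 2 legend gives it a calendar window of 4–6 months, and follow-up data come from the SEPHIA registry. Patients who leave the study or skip the program may still be tested. This stands as a reason to expect fewer losses, but it does not make the data complete.

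5. **The SD may be smaller than 20 W.** With the registry value of 15.6 W and 10 W, power is 95.7% with complete data, 93.6% at 10% missing, 90.7% at 20% and 87.7% at 27%. This is fair. However, the plan chose 20 W, and 40 patients from one centre cannot show that choice to be too cautious.

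**Conclusion.** The point holds in a limited form. The article states 90% power for 150 randomised patients and describes no allowance, in either arm, for patients without both tests, although it foresees dropout and offers the second test on completion of a program. On the printed 10 W and SD 20 W, an equal loss of 10% to 20% lowers power from 81.8% to between 77.6% and 72.6%, a cost of about 4 to 9 points. This rests on an assumed range, equal loss by arm, analysis of patients with both tests only, and 10 W taken as the difference tested.

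A reader might attribute the whole distance from 90% to missing tests. The documents do not support that: 8.2 points of it are present with complete data, because 150 does not follow from its own inputs. That is a separate and prior matter, and inflating 150 for missing tests would not restore 90%.

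**What to change.** Recruitment is complete, so leave N as it is.

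- **Power statement.** In the sample size section, say that the calculation assumed both ergometer tests in all 150 patients. Restate power for the number per arm expected to have both, or as a range (77.6% at 10% missing, 72.6% at 20%, with 68.2% at 27% as an upper bound). Reconcile the underlying calculation first.
- **Reporting.** Give the number with both tests by arm.
- **Primary analysis.** Replace the t test on patients with both tests by a likelihood-based or multiple-imputation analysis of the randomised patients, adjusting for t2 watts and centre. Patients without a t2 test can be kept through imputation.
- **Program participation.** Use it at most as an auxiliary variable in the imputation model, not as a covariate in the outcome model. It arises after randomisation, and the stated hypothesis is that the app improves adherence to exercise, so adjusting for it could remove part of the effect. The t2 test also follows inclusion, but it is already the plan's own reference point for the change.
- **Sensitivity analysis.** Add one in which missing t4 values depart from the main assumption.

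The cost is a less favourable power statement and a little more analysis work. No extra patients or visits are needed.

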## Methods/design

### Study design, setting, and patient characteristics

The study is an open-label multi-center randomized controlled trial. A total of 150 patients will be recruited from three CR centers based at university hospital clinics in Sweden (Fig. 1). Two of these are in the densely populated Skåne region (southern Sweden), while one is situated in the rural area of Norrland (northern Sweden). In total, approximately 1200 patients < 75 years of age are treated for acute MI at the three study centers each year. These patients will form the basis for the project cohort. Based on our feasibility study (see details in a subsequent section), we estimate that approximately 35% of patients screened for eligibility will be included in the study. As screening will not be done during weekends, holidays, or vacation high seasons, the recruitment is projected to take at least 1.5 years.

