### Outcomes

#### Primary outcome

The primary outcome, which the power calculations are based on, is change in submaximal exercise capacity (in watts, W) between the first and second physiotherapist visits. The submaximal exercise capacity, which reflects the patients’ level of physical fitness, is evaluated at two physiotherapist visits, the first at 2–4 weeks after discharge and the second when the patient performs the exercise program at the CR center, usually around 3–6 months post-discharge (Fig. 2). The test is performed on a bicycle ergometer according to the World Health Organization (WHO) protocol, with an increased workload of 25 W every 4.5 min [20, 21]. The initial starting load, 25 W or 50 W, is decided based on the patient’s exertion history. After 2 and 4 min of each workload, heart rate, perceived exertion according to Borg’s rating of perceived exertion (RPE) scale, and subjective symptoms, including chest pain and dyspnea according to Borg’s Category Ratio (CR-10) scale, are registered [22]. After 3 min, the systolic blood pressure is measured. The exercise test is discontinued at Borg RPE 17 and/or dyspnea 7 on Borg’s CR-10 scale.

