#### Secondary outcomes

The secondary outcomes are described as follows:Changes in the following variables measured from inclusion to first, second, and third nurse visits, respectively:Self-reported health using the visual analog scale (see Additional file 1)Healthy diet index as evaluated within SEPHIA (see Additional file 1)Smoking habits (self-reported)Weight (kilograms), body mass index (BMI, in kilograms/meter^2^), and waist circumference (in centimeters)Systolic and diastolic blood pressure (mmHg)Total cholesterol, low-density lipoprotein and high-density lipoprotein cholesterol, and triglycerides in plasmaFasting plasma glucose and HbA1cChanges in self-reported physical activity (by Haskell and Frändin and Grimby; see Additional file 1) measured from inclusion to first and second physiotherapist visits, respectively [23, 24]Uptake (proportion of patients who log on to the patient interface at least once) and adherence (proportion of patients registering data at least twice per week on a weekly basis throughout the intervention period)Number of telephone and physical contacts with the CR staffIncidence of cardiovascular events at 1 and 3 years after the index event: hospitalization for a new MI, heart failure or stroke, and cardiovascular deathCorrelations between self-reported physical activity levels and objective measurements of physical activity and sedentary time measured by a validated instrument for 7 consecutive days, as analyzed using ActiGraph accelerometers. ActiGraph accelerometers are widely used in research because they have shown high validity and reliability [25, 26]. The measurements will be performed in conjunction with the first and second physiotherapist visits (*t*2 and *t*4) on patients recruited at Skåne University Hospital in Malmö (*n* = 60).

As recruitment was finalized in April 2018 and patients are followed for 1 year, the final study results will first be available by the fall of 2019.

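### Continuous outcomes are tested as unadjusted change scores, and an open-ended rule then allows adjustment for whatever differences are observed, including visits and telephone contacts that arise after randomisation

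*Protocol article*

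**What the plan says.** Under Primary outcome, the protocol article defines the endpoint as "change in submaximal exercise capacity (in watts, W) between the first and second physiotherapist visits". Under Secondary outcomes, most continuous measures take the same form: "Changes in the following variables measured from inclusion to first, second, and third nurse visits, respectively".

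The section Statistical analysis, power, and sample size fixes the comparison: "Differences in outcomes between the control arm and intervention arm will be performed using an independent samples" t test for continuous variables, and a chi-square test for categorical ones. It then makes linear or logistic regression conditional. If the arms are seen to differ in baseline characteristics, in the number of follow-up visits or in telephone contacts, the analysis adjusts for those differences. The section does not say how large a difference must be, which variables are eligible, or whether the unadjusted or the adjusted estimate is the primary result.

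The planning inputs in the same section are "With a power of 90"%, "a two-sided significance level of 0.05", "a least mean difference at 10 W" and an SD of 20 W, with 50 control and 100 intervention patients.

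**The concern.** Two features of the stated rule matter.

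**The unadjusted change score.** Subtracting the first value in full fixes its coefficient at 1. Unless the two tests are almost perfectly correlated, this leaves avoidable noise in the comparison. If chance gives the arms different first-test values, part of that difference carries into the estimate through regression to the mean.

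**The trigger for adjustment.** In an open-label trial, a rule that adjusts for whatever is observed to differ lets the analyst decide, after seeing the data, whether to adjust, for what, and which result to lead with. It also covers variables that do not belong in the effect model. Visits and telephone contacts arise after randomisation. The section on the medical interface describes twice-weekly nurse review and targeted interventions, so the app may itself change contacts. Contacts with staff are also a listed secondary outcome. Adjusting for them can remove part of the effect that the trial is meant to measure.

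**Working it through.** **Inputs from the article:** difference 10 W, SD of change 20 W, two-sided 0.05, 50 and 100 patients. **Assumed:** the correlation rho between first and second watts, which the article does not give, and equal variances at the two tests.

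**1. The planned t test.** SE = 20 × √(1/50 + 1/100) = 3.46 W. The noncentrality is 10/3.46 = 2.89, and the noncentral t gives power 81.8%. The stated 90% is not reproduced: with these inputs and 1:2 allocation it needs 64 + 128 = 192 patients before any dilution. That is a separate matter and serves here only as the reference.

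**2. Adjusting for the first value.** With s the SD of watts at either test:
- Var(change) = 2s²(1 − rho)
- Var(adjusted) = s²(1 − rho²)
- Ratio = (1 + rho)/2

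| rho (assumed) | variance ratio | residual SD (W) | equivalent n for a change-score test | power for 10 W |
|---|---|---|---|---|
| t test on change | 1 | 20.0 | 150 | 81.8% |
| 0.6 | 0.80 | 17.9 | 150/0.80 = 188 | 89.4% |
| 0.8 | 0.90 | 19.0 | 150/0.90 = 167 | 85.6% |
| 0.9 | 0.95 | 19.5 | 150/0.95 = 158 | 83.7% |

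Over a wider range the same calculation gives 94.5% at rho 0.3 and 91.2% at rho 0.5.

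**3. Chance imbalance.** Given a first-test difference D between arms, the expected change-score estimate is the true effect minus (1 − rho)D. At rho 0.7, s = 20/√(2 × 0.3) = 25.8 W. A just-significant imbalance is about 1.96 × 25.8 × 0.173 = 8.8 W, which shifts the estimate by 0.3 × 8.8 = 2.6 W. In simulation with no effect (10,000 trials per rho), among trials with a significant first-test imbalance, the change-score t test rejected in 17.8%, 13.9% and 6.1% (rho 0.5, 0.7, 0.9). The adjusted model rejected in 4.5–5.0%.

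**4. The open choice.** In the same simulation, over all trials, type I error was:
- t test on change and adjusted model, each used alone: 4.5–5.4%
- a mechanically fixed trigger: 4.2–4.5%
- the better of the two p values, with a single covariate: 7.8%, 6.5% and 5.6% (rho 0.5, 0.7, 0.9)

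The inflation comes from freedom of choice, not from adjustment itself.

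**5. Adjusting for contacts.** Assume that the app shifts contacts by 1 SD and that 25%, 50% or 75% of a 10 W effect runs through them (3,000 simulated trials each). The adjusted estimate falls to about 7.5, 5.0 or 2.5 W. Power falls from about 82% to 50%, 26% or 10%.

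**The case against.** The strongest reply is that this is mainly a preference about efficiency. That is right for the t test. A reader might infer that the change-score analysis is biased or invalid. It is neither: randomisation makes it unbiased, and its overall type I error is nominal. Regression to the mean matters only given a chance imbalance. The gain for watts is about 2 to 8 power points and rests on an assumed correlation. At the registry SD of 15.6 W the planned test already has about 96% power for an undiluted 10 W.

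A second reply is that first-test watts may not be a true baseline. Patients are approached within 2 weeks of the infarction, preferably in the coronary care unit, and intervention patients may try the app during admission. The first ergometer test comes 2–4 weeks after discharge. This stands, and the fix must deal with it. It does not favour the current plan, because the change score subtracts that same value in full.

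Some wider readings are not supported:
- **Centre.** The article states "A total of 150 patients will be recruited from three CR centers", but it describes no stratification by centre and says the centres' follow-up is broadly alike. A centre term is ordinary content for the full plan.
- **Repeated visits.** Nothing states that patients with some visits missing are dropped. The abstract's wording on follow-up visits in the first year leaves open whether the 6–8 month laboratory values are used.
- **Laboratory values.** Weak correlation between inclusion and later values is plausible, but no figure in the article supports one.
- **Categorical outcomes.** Smoking goes to the chi-square test, so the change-score point does not cover it.

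None of these replies answers the trigger, which is stated text and not omitted detail.

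**Conclusion.** The point holds, as an improvement that should be made and not as a fatal flaw. The harm from the unadjusted change score is lost precision (5–20% more variance removed by adjustment if rho is 0.6–0.9) and sensitivity to chance imbalance in the first value. The harm from the trigger is more serious: the primary estimate is undefined, and the rule permits adjustment for post-randomisation visits and contacts. The size of that last harm depends on how much of the effect runs through contacts, which is unknown; the 25–75% shares are illustrations.

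A reader might also infer that adjustment for the first value rescues the trial's power. It does not. With the difference diluted to 6 W (10 × 0.6, for the 40% loss of adherence), power at SD 20 W is about 41% for the t test and only 43–57% after adjustment, over rho from 0.9 down to 0.3.

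**What to change.** Before any analysis by arm, and documented as such:

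1. Make the primary analysis a linear regression of second-test watts on arm and first-test watts, with patients in their allocated arm, used whatever imbalances appear. The arm coefficient is the same as from regressing the change on these terms, so the primary outcome keeps its meaning.
2. State that the first test may follow randomisation and first use of the app. Add a sensitivity analysis adjusting only for pre-randomisation covariates, named in advance.
3. Analyse the continuous secondary outcomes in the same way, adjusted for the inclusion value.
4. Delete the rule that adjusts when differences are observed. In no case adjust the effect estimate for visits or contacts; report these as outcomes.
5. Keep the t test on change as a supporting analysis.

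A centre term, and a mixed model that includes the 6–8 month laboratory values, are optional.

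No new measurement is needed and the visits are already scheduled. It would be wrong to say that all data were in hand: recruitment closed in April 2018 and the last nurse visit is at 12–14 months, so some follow-up was still due when the article appeared in January 2019. Second ergometer tests, usually around 3–6 months after discharge, would by then be largely complete, so the date of the change relative to any comparison by arm must be recorded. The remaining cost is a slightly less simple primary analysis.
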